#### Contextual considerations

The psychedelic experience comes with an increased sensitivity to internal and external stimuli. It follows that the general context of psychedelic administration fundamentally shapes drug response and hence safety, as well as potentially therapeutic efficacy [9, 88]. Contextual factors are commonly labeled as *the set and setting* [88]. The set refers to the participant’s mindset and includes the readiness, expectations, and intentions that one brings to the psychedelic experience, as well as any other preexisting psychological factors, including personality and psychopathology. The setting comprises the physical, social, and cultural environment surrounding the psychedelic experience. As soon as screening occurs, the first aspect of the set to be systematically considered in PAT trials consists of the psychiatric background of candidate participants. As mentioned in the study’s key exclusion criteria, individuals with a lifetime history of psychotic or bipolar disorders or with a family history of these conditions in first- or second-degree relatives are currently excluded from participation to prevent the risk of inducing a psychotic or a manic episode in those with these conditions or with a potential genetic vulnerability [9]. Further aspects of the set are addressed in the preparation sessions, whereas the setting is given specific attention during psychedelic administration. More details are provided below.

#### Preparation sessions

The main function of the sessions leading to psilocybin administration is to prepare participants for exposure to the substance [89] in terms of expectations, assumptions, readiness and intentionality [9, 88]. Our study includes two preparation sessions prior to the psilocybin administration session. The first session will take place two weeks into the inpatient alcohol detoxification program, and the second session will take place one day before the drug administration session (visit 6, day 20 +/-2). We provide the first preparation session two weeks into the detoxification program so that participants have already gone through the most intense withdrawal symptoms and have almost entirely tapered off from the benzodiazepines prescribed to manage these symptoms.

The principal aims of the two preparation sessions are as follows [85]:

To develop a therapeutic alliance between participants and therapists,To listen to the participant’s narrative of sAUD and treatment history to understand patterns of psychological inflexibility that are most prominent,To provide psychoeducation regarding psilocybin and its acute effects,To delineate the therapeutic boundaries, including regarding the use of therapeutic touch,To outline safety measures, including the rescue medications that can be used if necessary,To teach and practice grounding techniques, including diaphragmatic breathing, therapeutic touch and body scanning,To provide psychoeducation regarding the cognitive processes and behaviors that contribute to inflexibility from an ACT perspective and how one can shift from these patterns of inflexibility and associated maladaptive coping strategies toward processes that foster psychological flexibility through an interaction between the principles of ACT and the psilocybin experience,To assist the participant in setting an intention for the psilocybin session with the help of value cards to first identify important values.

#### Psilocybin dosing session

Psilocybin will be administered in a specifically dedicated room in the Brugmann University Hospital, decorated in a way that creates a warm and home-like atmosphere rather than a sterile clinical setting, thereby maximizing participant comfort [9]. The psilocybin session will be video-recorded for training (supervision) and safety purposes.

Participants will be dosed per os and receive either a high dose of psilocybin (30 mg) or a low dose of psilocybin (5 mg - active placebo) as determined by computer-generated randomization. They will be invited to lie comfortably on a bed, wearing eyeshades and headphones, and instructed to direct their attention toward their internal experience and ‘trust, let go, be open’ [90]. Through headphones, participants will be listening to a standardized music playlist, specifically curated to accompany the three principal intensity phases of the experience: the onset of psychoactive effects, the peak plateau, and the return to an ordinary state of consciousness [91].

After psilocybin administration, participants will remain under observation for 6–8 h, based on the drug’s duration of action [92]. Vital signs will be measured at 30 min intervals for the first 2 h and every hour thereafter until session completion. The assigned therapist-dyad will remain present throughout, and interactions with the participants will be supportive and nondirective.

Psychedelics generally intensify emotional experience and may give rise to anxiety, dysphoria, fear, panic, or paranoia [9]. Across PAT trials, the first response to psychological distress has been psychological support and reassurance, as well as therapeutic touch such as hand holding, according to preestablished individual boundaries. Participants may also be redirected to other grounding techniques practiced during the preparation sessions, namely, body scan and diaphragmatic breathing. Psychological support has generally been sufficient to address transient psychological distress across contemporary trials [13, 15, 35]. However, if insufficient, rescue medication will be available for one-time administration to treat anxiety [Temesta Expidet^TM^ (Lorazepam) 1-2.5 mg, sublingual] and acute psychosis posing a danger to the participant or others [Zyprexa Velotab^TM^ (Olanzapine) 5–10 mg sublingual]. Hypertensive urgency will be treated with captopril, 25–100 mg per os. Emergency treatment will be available on site.

#### Integration sessions

The psychotherapeutic sessions that follow the psilocybin experience aim to support its integration, “the process by which a psychedelic experience translates into positive changes in daily life” ( [93], p. 8). The therapists assist the participants in making sense of the psilocybin experience and deriving insights and learnings that can be implemented in their lives to improve mental health and general wellbeing, including reductions in drinking behavior. Our study includes two integration sessions, one day and one week after the psilocybin session.

The principal aims of the two integration sessions are as follows [85]:

To elicit a narrative of the participant’s psilocybin experience,To discern and examine facets of the participant’s experience that align with ACT principles, as well as occasions when the participant shifted closer to or farther from psychological flexibility,To further clarify values that are central for the participant by integrating the emerged material,To reflect on the extent to which the participant currently lives according to these values and on actionable ways to further reinforce committed action,To explore actionable ways to develop functional reinforcing coping mechanisms that may replace drinking behavior.

#### Concomitant care

The care as usual trajectory offered within the context of the inpatient alcohol detoxification program involves two weekly group therapy sessions around relapse prevention and psychosocial support and a one-time group therapy session around the influence of alcohol consumption on close relationships.

Concomitant interventions will be assessed at trial entry and during the study to control for confounds on study endpoint measures. Except for the use of lorazepam for the treatment of acute alcohol withdrawal syndrome, concomitant pharmacotherapy for sAUD is not allowed.

### Outcomes

#### Primary clinical outcome

The primary clinical outcome is the difference between the two treatment arms in terms of change from baseline (8 weeks to 1 day pre-enrollment) to 4 weeks posthospital discharge (1 day to 4 weeks postdischarge) in the percentage of heavy drinking days, defined as ≥ 5 standard drinks/60 g of alcohol for males and ≥ 4 standard drinks/48 g of alcohol for females [15]. A reduction in heavy drinking days yields clinically significant health ameliorations [94], matches the treatment objectives of numerous patients [95] and is recognized by the European Medicines Agency as an adequate measure of efficacy [96]. Moreover, previous results suggest that PAT might lead to a decrease in alcohol consumption without necessarily inducing complete abstinence [15, 54]. We opted for a primary clinical outcome measure at four weeks posthospital discharge to limit attrition, as well as because the literature suggests that at least 50% of patients resume excessive heavy drinking within the first month following an inpatient detoxification program [3, 97]. Longer term follow-up data will be collected up to six months posthospital discharge (see secondary outcomes). The TLFB [68] will be used to measure alcohol consumption. The TLFB is a semi-structured interview designed to assess daily alcohol (and other drug) use by obtaining estimates of quantity, frequency, and usage patterns within a specific timeframe. The tool has demonstrated adequate to excellent reliability and validity [98, 99]. See Table 1 for an overview of key outcomes and sampling time points.

#### Primary feasibility and safety outcomes

For full transparency on feasibility, we will report on both inclusion and retention rates. A consort diagram illustrating the participant retention rate during the recruitment, screening, and data collection stages will be presented. Demographic information and reasons for exclusion will be reported.

 [100] have drawn attention to a potential underreporting of adverse events in PAT studies due to a lack of systematic assessment and disclosure. To address this limitation, safety has been added as a primary outcome in our trial. Adverse events will be systematically recorded at each study visit and follow-up and reported in trial publications. They will be classified according to severity, causality, and whether they were expected or not.

#### Secondary clinical outcomes

The difference between both treatment arms with respect to change from baseline to 4 weeks (*) and six months (^▲^) posthospital discharge in terms of:

The percentage of heavy drinking days (^▲^) measured with the TLFB;The number of drinks per day (*,^▲^) measured with the TLFB;The percentage of days of abstinence (*, ^▲^) measured with the TLFB;Phosphatidyl-ethanol (PEth) blood concentration (*), which will serve as an objective marker of alcohol consumption [101] to corroborate the self-reported drinking data.As symptoms of anxiety, mood disorders, and trauma frequently co-occur with alcohol use disorders [18, 19, 102], we will assess changes in depression, anxiety, and trauma symptoms (*,^▲^) using the Beck Depression Inventory (BDI; [103]), the State-Trait Anxiety Inventory (STAI; [104], trait subscale), and the International Trauma Questionnaire (ITQ; [105]), respectively.To obtain a more global view of recovery, we will utilize a Patient Reported Outcome Measure (PROM), the Substance Use Recovery Evaluator (SURE; [106]) (*,^▲^), which assesses recovery from (drug and) alcohol dependence through a holistic lens by including the dimensions of drinking and drug use, self-care, relationships, material resources and outlook on life.

#### Neurocognitive mechanisms

The difference between both treatment arms with respect to change from baseline to one day and one week postpsilocybin dosing in terms of:

Neuroplasticity as assessed with the EEG-derived auditory long-term potentiation paradigm [66].EEG-derived alcohol cue reactivity [107].EEG-derived alcohol cue inhibition [107].

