#### Benzodiazepine discontinuation

Benzodiazepines with a short half-life (lorazepam [79]) will be used for the treatment of acute alcohol withdrawal syndrome upon admission in the inpatient alcohol detoxification program. The shorter half-life allows us to minimize the potential benzodiazepine-psilocybin interaction by ensuring a relatively lower lorazepam plasma concentration rapidly after full tapering off (at least 3 days before psilocybin administration), which is relevant, as benzodiazepines might blunt the psychedelic experience. The Clinical Institute Withdrawal Assessment Alcohol Scale Revised (CIWA-AR; [80]) will be used to assess withdrawal symptoms to ensure safe progressive lorazepam discontinuation, in line with evidence-based practice guidelines recommending individualized tapering off schedules with withdrawal scales [81]. In case full tapering off from lorazepam cannot be achieved within 17 days due to withdrawal symptoms, participants will be excluded from the study.

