#### Psychological processes and alcohol-related parameters

The difference between both treatment arms with respect to change from baseline to one week post-psilocybin administration, as well as four weeks, three and six months posthospital discharge on the following scales:

The Acceptance and Action Questionnaire II (AAQII; [110]) to assess the construct of psychological (in)flexibility.The Multidimensional Assessment of Interoceptive Awareness (MAIA; [111]) to evaluate interoceptive processes across 8 dimensions: noticing, trusting, not distracting, not worrying, attention regulation, emotional awareness, self-regulation, and body listening.The Watts Connectedness Scale (WCS; [63]) to measure felt connectedness to self, others, and the world.The Penn Alcohol Craving Scale (PACS; [112]) to assess the frequency, intensity, and duration of past-week cravings.The Alcohol Abstinence Self-Efficacy Scale (AASE; [113]) to evaluate participants’ confidence in their ability to resist drinking alcohol in high-risk situations.Readiness to change alcohol consumption behavior will be measured by collecting Likert-scale ratings of the participants’ (1) perception of the importance of change in drinking; (2) confidence in their ability to change; (3) readiness for change and (4) commitment to the goal of abstinence [15].

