#### Expectancy, blinding, and therapeutic alliance

Participants’ expectancy will be assessed with the Stanford Expectations of Treatment Scale (SETS; [114]) at baseline, and blinding efficacy will be assessed by asking participants and therapists to guess group allocation and indicate guess certainty following the psilocybin administration session. Furthermore, we will assess therapeutic alliance in both participants and therapists after the last preparation session with the Working Alliance Inventory-Short Revised (WAI-SR; [115]).

**Table 1 Tab1:** Schedule of key study activities

	Screening	Baseline	Preparation 1	Preparation 2	Dosing	Integration 1	Integration 2	4-week endpoint	6-month follow-up
**Days relative to dosing**		-20	-7	-1	0	+ 1	+ 7	+ 35	+ 190

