**Key outcomes**									
*Clinical outcomes*									
Heavy drinking		X						X	X
Drinking days		X						X	X
Abstinence		X						X	X
PEth								X	
Mood		X		X			X	X	X
Anxiety		X		X			X	X	X
Trauma		X		X			X	X	X
Global functioning		X						X	X
*Safety*									
Adverse events		X	X	X	X	X	X	X	X
*Feasibility*									
Insclusion rates	X								
Retention rates			X	X	X	X	X	X	X
*Neurocog. outcomes*									
Neuroplasticity (LTP)			X			X	X		
Cue reactivity			X			X	X		
Inhibition			X			X	X		
*Drug experience*									
Mystical (MEQ)					X				
Acceptance/Avoidance (APEQ)					X				
Trauma access/process. (Helioscope Q.)					X				
*Psychological processes*									
Flexibility (AAQQ II)		X		X			X	X	X
Interoception (MAIA)		X		X			X	X	X
Connectedness (WCS)		X		X			X	X	X
*Alcohol-related parameters*									
Craving (PACS)		X		X			X	X	X
Abstinence self-efficacy (AASE)		X		X			X	X	X
Readiness to change		X		X			X	X	X

*Abbreviations: PEth* Phosphatidylethanol, *LTP* Long-term potentiation, *MEQ* Mystical Experience Scale, *APEQ* Acceptance/Avoidance-Promoting Experiences Questionnaire, *AAQ-II* Acceptance and Action Questionnaire Version 2, *MAIA* Multidimensional Assessment of Interoceptive Awareness, *WCS* Watts Connectedness Scale, *PACS* Penn Alcohol Craving Scale, *AASE* Alcohol Abstinence Self-Efficacy Scale

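### EEG and symptom changes are anchored at days -7 and -20, when lorazepam and early withdrawal can add avoidable noise to the arm comparisons and confound the mechanism correlations

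*Protocol article*

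**What the plan says.** **Definitions.** Under Neurocognitive mechanisms, the three EEG outcomes are compared between arms as "change from baseline to one day and one week postpsilocybin dosing". Under Psychological processes and alcohol-related parameters, AAQ-II, MAIA, WCS, PACS, AASE and readiness are compared as "change from baseline to one week post-psilocybin administration, as well as four weeks, three and six months posthospital discharge". Under Secondary clinical outcomes, depression, anxiety and trauma are compared as "change from baseline to 4 weeks (*) and six months (^▲^) posthospital discharge".

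**Schedule (Table 1, row "Days relative to dosing").** The Baseline column is day -20. EEG is marked at Preparation 1 (day -7), Integration 1 (+1) and Integration 2 (+7), with no mark under Baseline or Preparation 2. Mood, anxiety, trauma, AAQ-II, MAIA, WCS, PACS, AASE and readiness are marked at day -20, at Preparation 2 (day -1), at +7 and at both later visits.

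**Lorazepam.** It starts on admission for acute withdrawal, with a taper individualised by withdrawal scale and completed at least 3 days before dosing. A participant is excluded if full taper "cannot be achieved within 17 days due to withdrawal symptoms" (Benzodiazepine discontinuation). At Preparation 1, participants are expected to "have almost entirely tapered off from the benzodiazepines prescribed to manage these symptoms" (Preparation sessions). One-time rescue lorazepam is permitted in the dosing session.

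**Use of the changes.** The secondary hypotheses predict that increases in neuroplasticity, flexibility and connectedness, and improvements in the alcohol-related parameters, will correlate with clinical outcome. Data analysis adds mediation analyses.

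**The concern.** The change scores are meant to capture what follows psilocybin. An anchor at admission, or during the last part of a benzodiazepine taper, also captures recovery from withdrawal, drug clearance, inpatient group therapy and the preparation sessions. Two things are at stake.

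- **Arm comparisons.** These extra sources of change are expected to be equal in both arms, so they add variance rather than bias. In a trial planned around 46 completers, avoidable variance in the secondary outcomes matters.
- **Correlations and mediation.** Randomisation does not protect an association between a participant's EEG or psychological change and that participant's later drinking. Because the taper follows withdrawal symptoms, lorazepam exposure at the day -7 EEG tracks withdrawal severity, which may also bear on relapse. An association read as mechanism could then partly reflect severity.

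**Working it through.** **1. The plan's own figure.** The plan gives no number for these outcomes. Its only sample-size figure concerns heavy drinking days. With λ = f²·N·m/(1 - ρ), m = 2, f = 0.25 and an assumed ρ = 0.5, N = 46 gives λ = 0.0625 × 46 × 2 / 0.5 = 11.5 and power 0.912. N = 44 gives 0.8997. Attrition: 46/0.75 = 61.3, rounded up to 62. Both stated figures reproduce. Their baseline is pre-admission drinking, so this point does not touch them.

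**2. Timeline.** Preparation 2 is visit 6, programme day 20 ± 2. Dosing is visit 7, one day later, so nominally day 21. Programme day = dosing day + Table 1 day. The latest end of taper is the earlier of day 17 and 3 days before dosing.

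| Dosing on programme day | Day -20 | Day -7 (EEG) | Day -1 | Latest permitted end of taper | EEG precedes that by |
|---|---|---|---|---|---|
| 19 | -1 | 12 | 18 | 16 | 4 days |
| 21 (nominal) | 1 | 14 | 20 | 17 | 3 days |
| 23 | 3 | 16 | 22 | 17 | 1 day |

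This assumes that the Table 1 offsets hold when the dosing day shifts. Across the window, the sole pre-dose EEG falls before the latest permitted end of taper. Day -1 falls at least 3 - 1 = 2 days after the last taper dose.

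**3. Post-dose recordings.** By the taper rule, day +1 is at least 4 days after the last taper dose. A participant given rescue lorazepam at dosing, however, has the +1 EEG the day after it. Lorazepam exposure can therefore differ between recordings in either direction.

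**4. Cost for the questionnaires.** Take the follow-up score as response and one earlier score as covariate. Residual variance is then σ²(1 - r²). Assumed correlations with follow-up are r = 0.3 from day -20 and r = 0.5 to 0.6 from day -1; the protocol gives none.

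- 0.3 to 0.5: (1 - 0.25)/(1 - 0.09) = 0.75/0.91 = 0.82, a fall of 18%.
- 0.3 to 0.6: (1 - 0.36)/(1 - 0.09) = 0.64/0.91 = 0.70, a fall of 30%.

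For an unadjusted change score with equal variances, the variance is 2σ²(1 - r): 1.4σ² at 0.3, 1.0σ² at 0.5 and 0.8σ² at 0.6. The falls are 29% and 43%. If day -1 does not correlate better with follow-up than day -20, this gain disappears.

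**5. EEG.** No magnitude can be given. The protocol states neither how many participants are still tapering at day -7 nor the size or direction of lorazepam's effect on these measures.

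**The case against.** - **The arm contrast is not biased.** A reader might infer that it is. Taper and withdrawal recovery are balanced in expectation, so the inference fails; the cost there is precision only.
- **Not everyone is on lorazepam at day -7.** Preparation 1 was placed two weeks in so that the worst of withdrawal is over, and day 17 is an exclusion limit rather than a typical taper end. This stands: only some participants may be affected.
- **Day -1 is not a pristine baseline.** It is free of taper lorazepam by rule, but nothing says withdrawal has resolved. It also follows nearly three weeks of inpatient care and Preparation 1, and past-week craving then describes a week in hospital. For recovery at 4 weeks and 6 months after discharge, admission is a legitimate reference. This stands, and it is why day -20 should be kept.
- **The SAP could already use day -1.** The protocol nowhere says that the value is discarded, and the word baseline cannot always mean the Baseline column, since EEG has no mark there. That is fair. But the article's definitions point to that column for the questionnaires, and naming the pre-dose value is a better method at almost no cost.
- **Lorazepam may already be covered.** Concomitant care says other interventions will be assessed to control confounding. Adjustment fits that intention, but the article does not tie it to the EEG.
- **The EEG need not move.** A reader might infer that it must. Moving it would put two recordings 2 days apart instead of 8 and lengthen the visit before dosing. With rescue lorazepam allowed, it still would not guarantee lorazepam-free contrasts. This stands.

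**Conclusion.** The point holds in a limited form. The schedule anchors the questionnaires at about admission and the EEG at a visit where some participants may be on or just off lorazepam. The randomised comparisons remain valid but noisier than they need be. For the questionnaires, the gain from the day -1 covariate is 18% to 30% of residual variance under the assumed correlations. The weaker part is inferential: correlations and mediation linking EEG or psychological change to drinking can be confounded by withdrawal severity and taper length, in a direction and amount the protocol does not allow one to state. The case is strongest for the EEG and for the 1-week post-dose contrasts, and weakest for post-discharge recovery. The affected outcomes are secondary or exploratory; the primary outcome is not involved.

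**What to change.** 1. **Questionnaires.** Keep day -20 as the descriptive and recovery reference. In the arm comparisons of BDI, STAI, ITQ, AAQ-II, MAIA, WCS, PACS, AASE and readiness, model the follow-up score with the day -1 value as pre-dose covariate. Day -20 may be added; with both in the model, analysing change from day -20 gives the same arm estimate. In the mechanism correlations use change from day -1, above all for the 1-week contrasts.
2. **EEG.** Record lorazepam dose and time since last dose at every EEG, including any rescue dose in the dosing session. Adjust EEG change, and its correlations with outcome, for exposure at the day -7 recording.
3. **Sensitivity analysis.** Repeat the EEG analyses without recordings made on or shortly after lorazepam. Rescue use occurs after dosing and may differ by arm, so this should remain a sensitivity analysis.
4. **Optional.** Move the pre-dose EEG to day -1 if the longer visit and the 2-day spacing are acceptable.

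Cost: items 1 to 3 need no new visit or recording, only exposure data at each EEG, some extra analysis and one or two degrees of freedom. They should be fixed before unmasking.
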